### Statistical analysis

All detailed statistical methods will be documented in a statistical analysis plan.

All analyses will be performed using either SAS software version 9.4 or later (SAS Institute Inc, Cary, NC, USA) or SPSS software version 26.0 or later (IBM Corp, Armonk, NY).

For tests between two groups, Fisher’s exact test will be used for dichotomous variables, Mantel–Haenszel Chi-square trend test for ordered categorical variables, Chi-square test for non-ordered categorical variables and Fisher’s nonparametric-permutation test for continuous variables. All efficacy evaluations will be adjusted for centre (strata in randomization) and gestational age (the most prominent risk factor). The difference between the two study arms with respect to binary outcomes such as the primary variable will be evaluated using logistic regression, for time-to-event data using Cox proportional hazards model, for number of recurrences per follow-up time using Poisson regression, for continuous outcomes using analysis of covariance (ANCOVA) or Fisher’s non-parametric permutation in case of not normally distributed data, and continuous outcomes repeatedly measured over time using mixed models for repeated measures.

All tests will be two-tailed. The primary analysis will be considered confirmed if *p* < 0.05.

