### Inclusion and exclusion criteria

Infants are eligible if they fulfil the following criteria:Infants born with a gestational age (GA) < 30 weeks.ROP stage 1 or stage 2 without plus disease in zone I.ROP stage 2 or stage 3 in posterior zone II without plus disease, with or without notch in zone I.ROP severity must be documented using wide-field digital imaging system photography (RetCam), and eligibility must be confirmed by at least two of three experienced paediatric ophthalmologists in the steering group.Signed informed consent by the parents/guardians (oral and written information).

The exclusion criteria are:Ongoing ocular infection.If the neonatologist or ophthalmologist considers the infant unsuitable for the study.

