### Eligibility, randomization and blinding

Infants evaluated for eligibility for enrollment in the study will be identified at routine ROP screening by the local ophthalmologist. ROP evaluations will adhere to clinical screening practice according to national guidelines. RetCam will be used at the ROP screening to document the extent of ROP disease, and images will be saved in the clinical record file. When the ROP screening ophthalmologist evaluates eligibility, the PI and the steering group will be contacted. Images will be evaluated, and eligibility for inclusion must be confirmed by at least two of three ophthalmologists in the steering group.

Parents/guardians will be given oral and written information about the study via the HOPE Parent Application (Addi Medical) and asked to participate if the infant is eligible. The signed informed consent will be collected before any study-specific data is reported and the infant is randomized. Randomization will be performed stratified by centre by a study nurse using an electronic application (HOPE). After randomization, the study nurse will provide eye drops to the assigned neonatal nurse in the neonatal intensive care unit (NICU) for administration or to the parents or guardians if the infant is discharged from the hospital. In case of problems regarding the study eye drops, a randomization list is safely stored in a locker at the NICU and available 24 h/day in case of emergency and safety issues. All investigators, ophthalmologists, staff, and patients/guardians, except pharmacists, are blind to the participants’ eye drop assignments. The single-dose containers for dexamethasone and placebo are similar, and identification of drop content will not be visible to an untrained eye.

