### Sample size

Natural history studies of ROP suggests that 50% of infants with ROP stage 2 in posterior zone II with haemorrhage or ROP stage 3 in zone II develop Type 1 ROP needing treatment [1]. We aim to reduce the number of infants progressing to severe ROP needing treatment with laser and/or anti-VEGF by 60%. Assuming 50% of infants need ROP treatment in the placebo group and 20% in the dexamethasone group, alpha 0.05, using a two-sided Fisher’s exact test, would require 45 infants to be included per study group (1:1 ratio), in total, 90 infants excluding dropouts, to achieve a power of 80%. Taking into account a 10% drop-out rate, five infants per study group and thus 100 infants in total will need to be included.

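### All efficacy analyses adjust for centre and gestational age only; ROP zone and stage at entry, already recorded before randomization, are left out, which forgoes a modest amount of power and leaves chance imbalance in entry severity unadjusted

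*Protocol article*

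**What the plan says.** The covariate set is stated in the Statistical analysis section: "All efficacy evaluations will be adjusted for centre (strata in randomization) and gestational age (the most prominent risk factor"). The model for the primary outcome is stated there too: "The difference between the two study arms with respect to binary outcomes such as the primary variable will be evaluated using logistic regression". Time to Type 1 ROP is to be analysed by Cox regression.

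Eligibility, randomization and blinding names one stratum: "Randomization will be performed stratified by centre by a study nurse". The same section, with Inclusion and exclusion criteria, requires wide-field photographs of the disease, and two of the three steering-group ophthalmologists must agree on eligibility.

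Eligibility covers several entry states. One is "ROP stage 1 or stage 2 without plus disease in zone I"; the other is stage 2 or 3 in posterior zone II without plus disease. Table 1 sets drop frequency by stage and zone, and its footnote defines Type 1 ROP by zone, stage and plus disease.

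Sample size takes its placebo rate from natural history: "50% of infants with ROP stage 2 in posterior zone II with haemorrhage or ROP stage 3 in zone II develop Type 1 ROP". It then plans on these terms: "Assuming 50% of infants need ROP treatment in the placebo group and 20% in the dexamethasone group", and "alpha 0.05, using a two-sided Fisher’s exact test, would require 45 infants to be included per study group (1:1 ratio").

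**The concern.** Gestational age is included because of its weight as a risk factor. But every enrolled infant is born before 30 weeks and already has ROP that meets a zone and stage criterion. The question is who progresses from there, and the route to the endpoint depends on where the infant starts. Under the footnote to Table 1, an infant with zone I stage 2 disease meets the endpoint on reaching stage 3, with or without plus disease. An infant with zone II stage 3 disease meets it only when plus disease appears.

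Entry zone and stage are therefore natural prognostic covariates, and they cost nothing to collect. As written, they are balanced neither by stratification nor by the model. If they predict progression, two things follow. The analysis has less power than the same data could give, and a chance difference between arms in entry severity goes into the estimate unadjusted.

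**Working it through.** **1. The plan's own figure.** Inputs from Sample size: 50% versus 20%, two-sided alpha 0.05, Fisher's exact test, 1:1. Exact enumeration gives power of 79.6% at 43 per group, 80.2% at 44 and 81.5% at 45. Dropout: 45 / 0.90 = 50 per group, 100 in total. The stated figure reproduces.

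**2. Expected events.** 45 × 0.50 + 45 × 0.20 = 22.5 + 9 = 31.5, about 32.

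**3. Chance imbalance in entry severity.** Assume half the infants are in the more severe category, with 45 per arm.
- SD of the between-arm difference in that share: sqrt(2 × 0.25 / 45) = 0.105.
- 95% limit: 1.96 × 0.105 = 0.21, or about 21 points.
- Exact binomial chance of a difference of at least 10, 15 or 20 points: 34%, 17% and 7%.
- Shift in the unadjusted risk difference = imbalance × risk gap between categories. At the 95% limit this is 1.96 × 0.105 × 0.30 = 6.2 points for an assumed gap of 30 points, and 1.96 × 0.105 × 0.50 = 10.3 points for a gap of 50. The planned difference is 50 − 20 = 30 points.

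**4. Power with two entry categories.** Assumptions: 45 per arm, four equal centres, gestational-age odds ratio 1.5 per SD, marginal rates held at 50% and 20%, likelihood-ratio test, 3,000 runs per row (Monte Carlo SE about 0.6 points). Placebo risks by category are assumed.

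| Placebo risk, severe / less severe | Share severe | Centre + GA | Entry category added | Gain (points) |
|---|---|---|---|---|
| 50% / 50% | 50% | 88.8% | 88.5% | −0.3 |
| 60% / 40% | 50% | 87.7% | 88.7% | 1.0 |
| 65% / 35% | 50% | 89.7% | 91.5% | 1.8 |
| 70% / 30% | 50% | 88.3% | 92.1% | 3.8 |
| 75% / 25% | 50% | 88.9% | 95.0% | 6.1 |
| 80% / 20% | 50% | 87.9% | 95.5% | 7.6 |
| 70% / 41% | 30% | 88.7% | 90.6% | 1.9 |
| 60% / 27% | 70% | 87.5% | 89.9% | 2.4 |

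With no treatment effect (2,000 runs per row), the rejection rate was 4.8–6.5% without entry category and 4.9–7.1% with it. The slight excess is a small-sample feature of both models and is not caused by the omission. It also means that a little of the largest gains is not real power.

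**5. Power with three equal entry categories, Firth-penalised likelihood-ratio test.** Assumptions: 90 infants, five centres, same gestational-age effect, 1,200 runs (SE about 1 point).

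| Placebo risks | Without | With | Gain (points) |
|---|---|---|---|
| not prognostic | 85.3% | 83.3% | −2.0 |
| 42 / 50 / 57% | 85.5% | 85.3% | −0.2 |
| 37 / 50 / 62% | 86.5% | 87.1% | 0.6 |
| 30 / 50 / 70% | 85.6% | 89.1% | 3.5 |
| 21 / 50 / 79% | 86.8% | 92.0% | 5.2 |

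A separate simulation gave gains of about 0 (no gradient), 1 (38/50/62%), 2 (30/50/70%) and 6 points (21/50/79%), in line with these tables.

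**The case against.** The strongest case against is that nothing here is wrong. A pre-specified logistic model with the stratification factor and one prognostic covariate is a sound analysis. A reader might infer from the omission that the trial is underpowered, biased or exposed to false positives. The documents support none of these. The sample size reproduces, the planned model reached about 85–90% in the simulations against a target of 80%, and leaving out a baseline covariate does not bias a randomized comparison. The standard error already allows for chance imbalance on average. That stands in full.

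A reader might also infer that the article shows progression to differ by entry category. It does not. Sample size gives one pooled rate for two groups, with none for zone I stage 1–2 or for posterior zone II stage 2 without haemorrhage. Table 1 gives those last two entry states the same schedule, so it implies no gradient between them. That entry category is prognostic is a reasonable inference from the endpoint definition, but the article does not quantify it.

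Nor can it be said that imbalance could mimic or hide most of the effect. Even at the 95% limit the shift is 6.2 / 30 to 10.3 / 30, about a fifth to a third of the planned difference. It is less if gestational age, already in the model, is correlated with entry severity.

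Finally, the article leaves detailed methods to a statistical analysis plan that is not shown and that might add covariates. This is secondary, because the article itself names the set for every efficacy evaluation. What survives is that a cheap, relevant baseline measurement is left unused.

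**Conclusion.** The point holds as a modest improvement in efficiency, not as an error. The planned analysis is valid and the stated power is met. Adding entry category would change power by about 0 points if it is not prognostic (down to about −2 with three categories and a penalised fit), by about 1 to 4 points for moderate gradients, and by about 5 to 8 for steep ones. It would also adjust for a chance imbalance that, at its 95% limit, is worth about 6 to 10 of the planned 30 points.

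All of these sizes rest on assumptions the documents cannot confirm: placebo risks by category, the share of infants in each category, the number of centres and the strength of gestational age. The facts that do stand in the article are that entry zone and stage are known before randomization, that they are part of the endpoint definition, and that neither the strata nor the model uses them.

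**What to change.** Before unblinding, add to the protocol or statistical analysis plan that the primary logistic model and the Cox model include, besides centre and gestational age, an infant-level entry ROP category. Define it from the worse eye, with two or three levels based on zone and stage (for example zone I stage 1–2, posterior zone II stage 2, posterior zone II stage 3). The definition should rest on the findings confirmed at eligibility.

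Cost: no new data. One or two extra parameters enter a model with about 32 expected events, so the categories must stay few, and power may fall slightly if entry category turns out not to matter. The worse-eye rule must be written, including how zone and stage rank against each other, because eligibility and drops are described by eye. Haemorrhage, which Sample size mentions, is not captured by zone and stage; the sponsor should decide whether to leave it out.

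A Firth-penalised fit is an optional and separate safeguard against small-sample error in a model with centre terms. In null simulations with 4 to 10 assumed centres, the ordinary Wald test rejected in 5.8–6.9% of trials and the Firth fit in 4.0–4.2%. The case for the covariate does not depend on it.

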### Ethical considerations

The protocol, informed consent form, and other written infant information have been submitted to the “Etikprövningsmyndigheten” (EPN, www.epn.se) in Sweden, (Ethical Dnr 2020–06028, Eudra-CT, 2020–004933 - 19 and CTIS, 2023–505318 - 97–00). The written unconditional approval was obtained prior to the study’s commencement and was forwarded to Thea Nordic, the manufacturer of the study medication, prior to shipment of study medication supplies to the centre. The study protocol has undergone independent peer-review to gain funding from a major external funding body.

## Discussion

This paper presents the DROPROP protocol: a prospective, randomized, multi-centre, double-blind trial designed to evaluate whether dexamethasone eye drops reduce the proportion of infants with severe ROP progressing to Type 1 ROP needing treatment compared to placebo. The findings of this study may impact the care of future preterm infants at risk of developing sight-threatening severe ROP worldwide.

As survival rates for preterm infants rise, the number of infants affected by sight-threatening ROP and needing ophthalmological expertise increases accordingly [2]. There is a concerning shortage of ophthalmologists available for ROP screening and treatment in many countries. We believe that dexamethasone eye drops could be a simple and low-cost treatment to reduce ophthalmological complications and lifelong visual impairment in these vulnerable new survivors. Research including preterm infants is challenging as they are particularly vulnerable and frequently experience critical illness and have uncertain prognoses [23]. Nevertheless, research is crucial, especially if it enhances our understanding or treatment of a medical condition [24]. Historically, clinical misadventures have occurred due to insufficient paediatric clinical research and off-label use of medications [25].

Research involving high-risk patients raises several ethical issues, particularly balancing potential risks and benefits. We acknowledge the safety concerns of topical dexamethasone intervention in our study. Intravenous or oral dexamethasone is commonly used in preterm care, i.e., to wean preterm infants from the ventilator and to prevent BPD. When used to prevent BPD, an initial high and then a tapering dose of 0.5 mg/kg per day of dexamethasone on the first day of life has been associated with an increased risk of cerebral palsy and impaired motor and cognitive development. However, treatment after one week of age and lower doses have not been shown to have the same adverse effects [21, 22]. The volume of a commercial eye drop is 50–75 µl, and the concentration of dexamethasone in Dexafree® eye drops is 1 mg/ml. Accordingly, we expose the infant to only 0.1–0.15 mg/day. Common ocular side effects of short-term topical dexamethasone are local discomfort during application and increased intraocular pressure, first noticed during the first two weeks of treatment (according to the product information of Dexafree®). We will, therefore, measure the intraocular pressure before and after one and two weeks of intervention and after ended intervention. Although systemic side effects are unlikely with the small doses of dexamethasone administered, we will closely monitor the infants’ weight and head circumference development as well as glucose levels in blood and urine during the intervention period and at 40 weeks PMA, a time point at which MRI of the brain will also be performed. We also address the risk of suppressed adrenal function and reduced endogenous cortisol production during intervention. Therefore, we collect saliva samples for cortisol measurement before and after intervention, weekly during intervention, and follow-ups at 2 and 5.5 years of age. We consider the use of local eye drops with a low dose of dexamethasone for a limited period (one to 12 weeks) to pose less risk to the infant than general anesthesia, laser and/or anti-VEGF treatment. The benefits of reducing potential risks associated with general anesthesia and destructive laser treatment, as well as exposing infants to anti-VEGF with unknown systemic effects, are substantial. Multiple studies have shown that infants treated for ROP have the poorest visual and cognitive outcomes [26, 27]. It is also well known that infants treated for ROP with laser and/or anti-VEGF have a higher risk for blindness than not developing ROP needing treatment [28, 29]. Both general anaesthesia and anti-VEGF-treatment are suspected to affect brain development [12, 30], and laser treatment is a destructive treatment that damages the peripheral retina [11].

In conclusion, we conduct this study to evaluate the effectiveness and safety of dexamethasone eye drops as a preventative therapy for preterm infants with severe ROP. The findings from our study aim to support clinical practice and national guidelines to provide the best care for this particularly vulnerable group of infants worldwide. We believe that our research has the potential to significantly benefit children by reducing the risk for visual impairments, thereby improving their quality of life.

We plan to publish the results of this study in peer-reviewed journals and present data at national and international conferences.

## Data Availability

No datasets were generated or analysed during the current study.

## Abbreviations

AE: Adverse Event
BPD: Bronchopulmonary Dysplasia
CRF: Case Report Form
DMC: Data Monitoring Committee
GA: Gestational Age
IVH: Intraventricular haemorrhage
NEC: Necrotizing enterocolitis
MRI: Magnetic Resonance Imaging
NICU: Neonatal Intensive Care Unit
PDA: Patent Ductus
PMA: Postmenstrual Age
ROP: Retinopathy of Prematurity
SAE: Serious Adverse Event
SpO2: Oxygen saturation
